### Recruitment of participants to the trial

The school health services will identify children aged 6–12 years with overweight and obesity during routine health and growth checks and inform the parents about the ongoing study and possibility of participating. Likewise, PHC and PC can recruit eligible participants to the trial. A conditional incentive (gift voucher worth €85) will be provided after the end of the study to reimburse parents for the time they spent on study-related activities. A written informed consent will be obtained from all parents by a research assistant via REDCap or via post and prepaid envelopes. Written consent will be obtained from both parents when applicable, even if only one of them participates in the study. Children will be informed about the study by their parent(s) and asked whether they agree to the collection of height, weight and waist measurements. Participation is voluntary, and parents will be informed that they can withdraw at any time without explanation.

### Inclusion and exclusion criteria for the trial

Eligible participants are parents of children between 6 and 12 years of age who have children with overweight or obesity according to IOTF criteria [43]. Children taking medication affecting weight development will be excluded from the study. Families in the intervention group are advised not to participate in other forms of structured treatment during the study period. The ML group sessions will be conducted in easy Swedish and potentially in other languages depending on needs.

### Sample size

We estimate that the trial will need 126 children (63 children in the intervention and 63 in the control group) to be able to detect a difference at 12 months between the groups in BMI z-score of -0.16 with a standard deviation of 0.3, 80% power and an alpha level of 0.05, including an estimated 10% loss to follow-up.

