### Intervention arm: the ML program

Families in the intervention arm will receive the 12-month ML group-based program. Over the study period (January 2026 – December 2028), two ML groups will be initiated every six months, each including 6–10 parents. Group sessions will be offered weekly, either face-to-face at PHC clinics or online, while booster sessions will be provided by phone or videocall. If a parent misses a session, a follow-up call is offered. If a parent does not attend any of the first three sessions, they will be invited to join the next available group in the study.

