### Randomization

When parents have signed the consent form, they will be randomized to a treatment arm using REDCap randomization module [61]. A block randomization with a block size of six will be used to ensure a balanced allocation across treatment arms within each stratum. Stratification into the two strata overweight and obesity will be performed based on the baseline BMI z-score. Each block of six will have three participants in the intervention arm and three in the control arm, and the order of assignments within each block will be random. To include 126 participants, 21 blocks are needed. A research assistant will inform the clinics about which arm the participant belongs to. Neither HCPs nor parents will be blinded to allocation. The statistician remains blinded to group allocation until the analyses are performed to ensure objectivity. HCPs will not have access to the random allocation sequence.

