### Data analysis

All analyses will be performed as an intention-to-treat analysis. Descriptive statistics will be used to summarize participant characteristics at baseline per study arm. Prior to analysis, the distribution of the outcomes will be assessed for normality and homogeneity. Between arm differences for outcomes, BMI z-score (primary outcome), %IOTF-25, probability of reaching BMI z-score cut-offs and WHtR will be analyzed.

To analyse the primary outcome of BMI z-score we will fit a linear mixed model with BMI z-score at 0, 3, and 12 months as the outcome variable, including a random intercept for each child. Fixed covariates will be treatment assignment (ML or control), time (in months), their interaction, and baseline weight status. The effect of the treatment will be assessed by the interaction parameter, which is interpreted as the difference in change of BMI z-score per month” between the two randomisation arms. A dose-effect analysis will be performed to assess the effect of number of ML sessions attended. This will be performed by replacing the treatment variable in the regression model with a variable indicating how many sessions the child’s parents attended.

The register control arm will be compared against the ML arm regarding BMI z-score, %IOTF-25, probability of reaching BMI z-score cut-offs and WHtR, using the same methods as described above adjusted for confounders. Secondary outcomes will be analyzed using the same principles as above. Interviews with parents and HCP will be transcribed verbatim and analyzed using reflexive thematic analysis [73–75]. We will explore causal pathways between effectiveness- and implementation outcomes by integrating the quantitative and qualitative data. Missing data will be evaluated for its extent and patterns. If missingness in key outcomes (e.g., BMI z-score, %IOTF-25, BMI z-score cut-offs, WHtR) exceeds a predefined threshold, appropriate statistical methods such as multiple imputation will be applied. Full details about the analysis will be described in the Statistical Analysis Plan, which will be finalized and published in Clinicaltrials.gov before the end of data collection.

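### ML is delivered in parent groups, but the sample size and the stated primary model treat all children as independent

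*Protocol article*

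**What the plan says.** The Sample size section of the protocol article gives the total: "We estimate that the trial will need 126 children (63 children in the intervention and 63 in the control group". The target is a "difference at 12 months between the groups in BMI z-score of -0.16 with a standard deviation of 0.3". Power is set at 80% and the significance level at 0.05, and the total already allows for one child in ten being lost. No intraclass correlation, design effect or group is mentioned.

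Allocation is individual and balanced (Randomization): "Each block of six will have three participants in the intervention arm and three in the control arm".

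Delivery differs between the arms. In the ML arm, "two ML groups will be initiated every six months, each including 6–10 parents". The section on the Co-Fam model describes ten weekly 90-minute group sessions in which role play and peer discussion are key components, followed by six individual booster sessions. The control arm receives guideline-based standard care, and no study groups are formed there.

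The Data analysis section describes a linear mixed model that takes BMI z-score from all three visits (baseline, month 3, month 12). The score enters "as the outcome variable, including a random intercept for each child". The fixed terms are treatment, time, their interaction and baseline weight status. The treatment effect is read from the interaction. There is no term for ML group or group leader.

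**The concern.** Children are randomised one by one, but those in the ML arm are then treated through shared groups. Parents in a group have the same sessions, leaders and discussion, so their children's changes in BMI z-score may be more alike than those of children in different groups. Nothing comparable is set up for controls. This is a partially nested design, with clustering in one arm.

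The child random intercept handles repeated measurements on one child. It does not absorb correlation between children whose parents share a group. If that correlation is positive, two things follow: the standard error of the treatment effect is too small, so the test rejects too often when ML has no effect; and the trial has less power than stated. The first matters more, because it bears on the validity of the primary test and favours declaring ML effective.

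The article leaves full analysis details to a later SAP. It does, however, already state the random-effects structure and the sample size, and both assume independence.

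**Working it through.** **Inputs from the protocol.** Difference 0.16, SD 0.3, power 80%, alpha 0.05 (taken as two-sided), 10% loss, 63 per arm, groups of 6–10 parents.

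**Assumed.** ICC 0.02, 0.05 and 0.10, because the protocol gives none.

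**1. The plan's own figure.** n per arm = 2 × (1.96 + 0.8416)² × (0.3/0.16)² = 55.2, rounded up to 56. Then 56/0.9 = 62.2, rounded up to 63 per arm, or 126. This is an exact match with independent children, so the calculation has no allowance for clustering.

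**2. Power without clustering.** Completers per arm: 63 × 0.9 = 56.7. SE = 0.3 × √(2/56.7) = 0.0563. Power = Φ(0.16/0.0563 − 1.96) = 81%. Rounding leaves about one point of slack.

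**3. Clustering in the ML arm only.** With m children per group at the start and 10% loss:
- DEFF = 1 + (0.9m − 1) × ICC
- SE = 0.3 × √[(1 + DEFF)/56.7]
- normal-approximation power = Φ(0.16/SE − 1.96)
- type I error of a test that ignores groups = 2 × [1 − Φ(1.96 × 0.0563/SE)]
- Satterthwaite df = (vT + vC)² / [vT²/(G − 1) + vC²/55.7], where vT = 0.09 × DEFF/56.7, vC = 0.09/56.7 and G = 56.7/(0.9m); power is then taken from the noncentral t distribution.

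For m = 8 (0.9m = 7.2, G = 7.9):

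| ICC | DEFF | SE | Power, normal | df | Power, Satterthwaite | Type I, groups ignored |
|---|---|---|---|---|---|---|
| 0.02 | 1.124 | 0.0581 | 79% | 22.4 | 75% | 5.7% |
| 0.05 | 1.310 | 0.0605 | 75% | 19.9 | 71% | 6.8% |
| 0.10 | 1.620 | 0.0645 | 70% | 17.2 | 65% | 8.7% |

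By the normal approximation, the difference detectable with 80% power is 2.8016 × SE: 0.170 at ICC 0.05 and 0.181 at ICC 0.10, against 0.16 planned.

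**4. Other group sizes.** Normal-approximation power at ICC 0.02, 0.05 and 0.10 is 79%, 77% and 73% for m = 6, and 78%, 74% and 67% for m = 10. Type I error at ICC 0.10 is 7.6% and 9.8% respectively.

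**5. Favourable cases.** At ICC 0.01, power is 80.2% for m = 6 and 79.9% for m = 8. With m = 3 or 4 and ICC 0.05, power is about 79% (78% and 77% with Satterthwaite) and type I error is 5.5% to 5.8%.

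**6. Which m is likely.** Under Secondary outcomes, the protocol plans interviews with two to three parents from each ML group, about 16 in all. That implies 16/3 = 5.3 to 16/2 = 8 groups. With 8 groups, 63/8 = 7.9 children per group, which is why m = 8 is the central case.

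**The case against.** Most of the case on the other side concerns size, and much of it stands.

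- **The ICC is assumed.** At 0.02 or below, the loss by the normal approximation is about one or two points. Nothing in the protocol supports a particular value for BMI z-score at 12 months, and nine months of individual boosters may weaken the group correlation by then.
- **Groups are counted in parents.** The Discussion says that both parents are encouraged to attend, so a group of 6–10 parents may hold fewer children. This stands, and step 5 shows its effect. The planned interview numbers point nearer to 8 children per group.
- **The figures come from a two-sample comparison at 12 months.** The planned test is a treatment-by-time interaction over three visits, and its power and type I error were not derived. Baseline and repeated measures may recover some precision. That helps power but does not correct a standard error that ignores groups.
- **The arms are not wholly different.** Table 1 lists parental support programs within obesity care, and the Discussion says that ML group leaders serve both arms. A leader effect may therefore partly cancel. The shared sessions and peer discussion remain specific to ML.
- **The SAP could add a group term.** It could, but the model as published does not have one.

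A reader might infer that any positive correlation takes power below 80%. It does not: the rounding slack holds 80% at ICC 0.01 with groups of 6 by the normal approximation. A reader might also infer that siblings would be analysed as independent, because no rule limits a family to one child. The protocol does not say that siblings are enrolled, and a condensed article may omit such a rule, so no finding rests on that silence.

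**Conclusion.** The point holds in conditional form. The sample size of 126 and the stated primary model both assume independent children, in a design where one arm is treated in groups. If outcomes are positively correlated within ML groups, the standard error is too small, and power is overstated once the rounding slack is used up.

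The size depends on two quantities that the protocol does not give: the ICC and the number of children per group. It runs from negligible (ICC about 0.01, or few children per group) to material. At ICC 0.05 to 0.10 with groups of 8, power falls to the 65–75% range, depending on the ICC and the degrees of freedom used, and a test that ignores groups has a type I error of about 7% to 9%. These figures assume clustering in the ML arm only, equal group sizes, 10% loss and the two-sample approximation. They indicate scale and are not the operating characteristics of the planned interaction test.

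**What to change.** Before the SAP is finalised:

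1. Add a random effect for ML group to the primary model, in the ML arm only, with Satterthwaite or Kenward-Roger degrees of freedom. Let it act on change over time. The treatment effect is a difference in slopes, so a group intercept that is constant over time would not carry the correlation that matters.
2. Make sure that ML group membership is in the analysis dataset. Parents who miss the first three sessions can be invited to a later group, so state whether the first assigned or the attended group defines membership.
3. Restate the power of 126 children, or the detectable difference, over a range of ICCs and of children per group. Compute it with the same small-sample degrees of freedom as the analysis. For groups of 8 at ICC 0.05, for example, quote about 71% and not the normal-approximation 75%.

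The cost is SAP wording, one variable in the dataset, a less favourable stated power and a somewhat wider confidence interval. No extra children are needed and treatment does not change.

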### Implementation of the Co-Fam model

An Implementation Research Logic Model (IRLM) [56] was developed during the exploration and preparation phase through a co-design process involving parents and personnel from PHC, PC and school health services, conducted in a series of workshops. This process is described in detail in a separate paper [29]. The hypothesized relations between determinants, strategies and mechanisms are shown in Fig. 3. Implementation strategies based on the Expert Recommendation for Implementing Change (ERIC) taxonomy [57, 58] and their form and function [59] were discussed and approved by HCP to ensure contextual and clinical feasibility. The IRLM includes determinants in the outer context, inner context, bridging factors and innovative factors based on the EPIS framework [27]. Mechanisms of change of the strategies were hypothesized based on the Capability, Opportunity, Motivation and Behaviour (COM-B) model and the Theoretical Domains Framework (TDF) [60]. Outcomes refer to effectiveness of the ML program and of implementation of the Co-Fam model. The HSS components and related implementation strategies have been evaluated previously [46].

**Fig. 3 Fig3:**
[figure not shown]
Implementation Research Logic Model. Determinants are marked as a barrier (-) or facilitator (+). Strategies are linked to determinants and mechanisms through footnotes. Mechanisms are based on COM-B and the Theoretical Domains framework. Abbreviations: ML, More and Less; HCP, Health Care Personnel; BMI, Body Mass Index; IOTF, International Obesity Task Force, T2D, Type 2 diabetes

### The implementation strategies

The strategy *Conduct ongoing training* is a four-day course for HCPs in the ML program based on a manual, including supervision and feedback. The strategy *Prepare parents to be active participants* includes HCPs providing information to families meeting the inclusion criteria about consequences of overweight in children and the ML program. The strategy *Intervene with parents to enhance uptake and adherence* includes HCPs distributing information leaflets in different languages to support recruitment and contact with civil organizations within the community to increase uptake of hard-to-reach groups. The strategy *Create a learning collaborative* includes meetings of the research team together with HCPs from PHC and school health services every six months to discuss study progress and potential problems. The strategy *Promote adaptability* enables revision of strategies if needed (while keeping the intervention components intact), to be agreed on during the learning collaborative meetings. The strategies *Remind clinicians* and *Conduct educational outreach visits* aim to support HCPs during implementation. Reminders include newsletters sent four times per year with updates about the study and useful tips for recruitment and meetings with families. Outreach visits include inspirational lectures for HCP on two occasions per year. Implementation strategies are described in more detail elsewhere [29].

### Randomization

When parents have signed the consent form, they will be randomized to a treatment arm using REDCap randomization module [61]. A block randomization with a block size of six will be used to ensure a balanced allocation across treatment arms within each stratum. Stratification into the two strata overweight and obesity will be performed based on the baseline BMI z-score. Each block of six will have three participants in the intervention arm and three in the control arm, and the order of assignments within each block will be random. To include 126 participants, 21 blocks are needed. A research assistant will inform the clinics about which arm the participant belongs to. Neither HCPs nor parents will be blinded to allocation. The statistician remains blinded to group allocation until the analyses are performed to ensure objectivity. HCPs will not have access to the random allocation sequence.

### Primary outcomes

The primary outcomes, BMI z-score and %IOTF-25, will be assessed at baseline, after three and 12 months for both arms. The BMI z-score is calculated based on age- and sex-specific IOTF reference data [43]. The %IOTF-25 is a percentage-based index of children above the IOTF threshold for overweight. Combining it with the BMI z-score may be better suited to follow changes in weight for children and adolescents with obesity [62].

The primary implementation outcome is fidelity to the ML program. Dose delivered is measured by number of ML group sessions and booster sessions delivered while dose received is measured by average number of ML group sessions and booster sessions received per participant. Adaptations made to the sessions during the trial and reasons for adaptations will be documented by asking ML group leaders after each completed group. Efforts to increase program fidelity include supervision of ML group leaders during their first ML group by the trainers. Participant responsiveness will be evaluated through questionnaires at week five and ten of the ML program and through interviews after the ML program is finalized.

### Secondary outcomes

The probability of reaching a reduction in BMI z-score cut-offs of ≥ 0.25 or ≥ 0.5 will be used as they indicate a clinically significant reduction in BMI [63]. Waist-to-height ratio (WHtR) will be compared between groups to estimate excess adiposity [64]. The child’s dietary habits will be assessed through the validated Eating and Physical Activity Questionnaire (EPAQ) [65] using nine questions on dietary habits. Parents are asked to recall the child’s intake of unhealthy and healthy foods and unhealthy drinks. Questions are answered as amounts of each item (deciliters, glasses or portions) from 0 to 7 or more. The child’s physical activity level will be assessed through three questions asked to the parents [66]. Questions are answered by estimating the number of days of physical activity per week (0–7), number of times of exercise per week (0–7) and the proportion of time spent sedentary during the week (0–5). The child’s eating behavior will be assessed using the validated Children’s Eating Behavior Questionnaire (CEBQ) [67] answered by a parent. It consists of 35 questions on eight scales that identify behavioral traits that may contribute to obesity or disordered eating. Parents rate their child’s eating behavior on a five-point Likert scale (never, rarely, sometimes, often, always). Parental feeding practices will be measured using the validated Comprehensive Parental Feeding Questionnaire (CPFQ) [68, 69] including five factors: Monitoring of children’s food intake, pressure to eat, restriction of food, use of food for emotional regulation, and healthy eating guidance. It is comprised of 36 questions in which parents rate their feeding practices on a four-point Likert scale (rarely, sometimes, often, very often) or (disagree, somewhat disagree, somewhat agree, agree). Potential adverse events could be rapid weight loss, sudden unhealthy change in eating behavior and/or physical activity. This will be monitored continuously and affected families will be guided to appropriate care.

Fidelity to implementation strategies will be assessed as described in Table 3. Potential adaptations to implementation strategies should support sustainability to ensure that the ML program can be integrated into routine practices when the study is commenced [70, 71]. If any adaptations to implementation strategies are suggested by the HCPs, the Model for Adaptation Design and Impact (MADI) will be used to decide if an adaptation is needed and evaluate the adaptation. MADI involves a description of what is modified, nature of adaptation, who participated in adaptation decision-making, for whom the adaptation was made, and when the adaptation occurred [71].

**Table 3 Tab3:** Assessment of fidelity to the implementation strategies based on a checklist, survey and interviews

Strategy	Fidelity dimension	Assessment	Method/ Performed by
Conduct ongoing training	Adherence	Number of training opportunities offered to HCP and number of participants in ML training	Checklist by researchers
	Responsiveness	Survey at the end of the ML training	Survey to ML group leaders
Prepare parents to be active participants	Adherence	Number and type of activities performed by HCP to motivate parents to be active in ML sessions	Checklist by researchers, survey to HCP
	Responsiveness	Individual interviews with parents about their motivation to participate and school nurses about the referral process	Interviews by researchers
Intervene with parents to enhance uptake & adherence	Adherence	Number and type of activities performed in the community to motivate parents to be active	Checklist by researchers
	Responsiveness	Individual interviews with parents, school nurses and civil organizations in the community about uptake and engagement	Interviews by researchers
Create a learning collaborative	Adherence	Number of learning collaborative meetings for HCP and number of participants	Checklist by researchers
	Responsiveness	Interviews with healthcare personnel about the usefulness of the collaborative meetings	Interviews by researchers
Promote adaptability	Adherence	Number of adaptations requested, evaluated and made	Checklist by researchers
	Responsiveness	Interviews with healthcare personnel evaluating potential adaptations	Interviews by researchers
Remind clinicians	Adherence	Number of newsletters sent to HCP	Checklist by researchers
	Responsiveness	Individual interviews with HCP about the content of the reminders and their usefulness	Interviews by researchers
Conduct educational outreach visits	Adherence	Number of outreach visits and attendance	Checklist by researchers
	Responsiveness	Individual interviews with healthcare personnel about the usefulness, content and appreciation of the outreach visits	Interviews by researchers

*Abbreviations:**HCP* Healthcare personnel, *ML* More and Less

Acceptability is the perception among stakeholders that a given treatment, service, practice, or innovation is agreeable, palatable, or satisfactory [72], while feasibility is the extent to which a new treatment or an innovation can be successfully used or carried out in a given setting [72]. Acceptability and feasibility will be evaluated with individual interviews with approximately two to three parents from each ML group (total ~ 16 parents) three to 12-months after start, and with providers at the end of the 24-month follow-up.

A health economic evaluation of the Co-Fam model will be conducted using a cost-utility design, applying a decision tree and Markov model over a lifetime horizon. The model will be driven by changes in BMI resulting from the trial. Costs will be obtained from the Co-Fam model and the ML program, supplemented with data from the literature and other publicly available sources. Additional parameters, including transition probabilities and utility weights for different health statuses will be derived from both the literature and intervention data. Quality-adjusted life years (QALY) will serve as the measure for utility. Cost-effectiveness will be expressed as an incremental cost-effectiveness ratio (ICER). Sensitivity analyses will be performed to assess the robustness of the results to plausible variations in key parameters and assumptions.

